## Abstract

**Background:**

Frailty is considered a major public health challenge of the 21st century, characterized by the decline of multiform body functions. Physical activity may be the most effective intervention to delay frailty. This study aims to verify the effect of remotely supervised physical activity on health profile in community-dwelling frail older adults.

**Design:**

This is a multicenter, three-blind, two-arm, and cohort randomized controlled study.

**Methods:**

The intelligent exercise rehabilitation management system (IERMS) is an integrated digital platform that involves evaluation, guidance, monitoring, and feedback. A total of 120 participants aged ≥ 65 years and diagnosed as frailty on the FRAIL scale will be recruited and randomly divided into two groups. Group 1 will receive a 12-week IERMS-based intervention, and Group 2 will receive the usual care. Data will be collected at baseline, 12 and 24 weeks. The primary outcome is the physical function, and secondary outcomes include gait parameters, psychology, and cognition measurements. Analyses will be performed using DSS statistics, version 25. *P* < 0.05 will be considered statistically significant.

**Conclusion:**

We believe that intervention plays a positive role in delaying the frailty. If our program is effective, we will provide a viable means to promote healthy aging in primary healthcare.

**Trial registration number:**

ChiCTR2100052286; Pre-results.

## Introduction

Frailty is a kind of clinical syndrome in older adults who are easily affected by stress. Physical frailty, originally defined by Fried et al. (2001), includes slow gait speed, weakness, self-reported exhaustion, low activity, and weight loss. Due to differences in regions, diagnostic criteria, and other factors, the prevalence of frailty is changed in different parts of the world; previous studies have shown that the prevalence ranged from 4 to 59% and increased with age (Choi et al., 2015; Hoogendijk et al., 2019). It is associated with the development of most chronic diseases, falls, fractures, disabilities, and other adverse outcomes (Theou et al., 2017; Hanlon et al., 2018). Fortunately, frailty is a dynamic reversible process, and measures can be taken to prevent it in advance (Lang et al., 2009).

The health benefits of physical activity have been widely recognized (Cheng et al., 2021). Proper physical activity can improve muscle, heart, and lung function and reduce the risk of high blood pressure, coronary heart disease, stroke, diabetes, cancer, depression, sleep disorders, falls, and fracture (de Labra et al., 2015; Dipietro et al., 2019; Mugueta-Aguinaga and Garcia-Zapirain, 2019). The WHO recommends that adults over 65 years of age engage in at least 150 min of moderate-intensity physical activity per week or at least 75 min of vigorous-intensity physical activity per week, or a combination of moderate and vigorous-intensity physical activity to achieve this amount of physical activity, with at least 10 min of continuous activity each time (van der Ploeg and Bull, 2020).

Recent research has found that physical activity may be the most effective intervention for frailty (Cheng et al., 2021). It is much more accomplished and effective when performed under supervision (Bonnefoy et al., 2012). Home-based supervised training has a better effect on strength and physical function and is more intense (Lacroix et al., 2017; Suikkanen et al., 2021). However, the allocation of health technicians is far from meeting the requirements of the training supervised by physiotherapists at home, so the current focus of primary healthcare is how to maximize the use of existing medical resources and benefit more people. Remote supervision based on wearable devices gradually attracts the attention of researchers (Garcia-Moreno et al., 2020; Zacharaki et al., 2020). This study aims to verify the effect of remotely supervised physical activity on health profile and observe the lingering effect in community-dwelling frail older adults.

## Methods

This study was designed and will be conducted and reported in keeping with the Consolidation Standards of Reporting (CONSORT) 2010 statement (Eldridge et al., 2016).

### Platform Delivery

The intelligent exercise rehabilitation management system (IERMS) was designed and developed by the research group independently (Xu et al., 2020). It is an integrating evaluation, guidance, monitoring, and feedback of an integrated intelligent motion rehabilitation management system. It consists of three parts: sensing device layer, management data layer, and application layer. The sensing layer collects the health data, including smart insoles, bracelets, and other common terminals; the management layer conducts data processing; and the application layer visualizes the health results, including websites, applications, and applets. Smart insole is a kind of sensing device that contains eight inertial and thin-film pressure sensors (FSR 400) and grants China an invention patent (Publication Patent Number: 201810114305.3).

### Study Design

A three-blind, two-arm, cohort randomized controlled trial will be conducted to evaluate the effects of IERMS-based physical activity on health performance in frail older adults (Registration number: ChiCTR2100052286)^1^. A total of 120 participants will be recruited according to the screening criteria from six community health service centers in Changchun, China, and the participants will be randomly divided into two groups. Participants in the first group will receive a 12-week IERMS-based intervention, and participants in the second group will receive a 12-week conventional care. Then, there will be a 12-week follow-up. Data will be collected at baseline, 12 and 24 weeks. The study design is shown in Figure 1. After the intervention, the same guidance will be given to the second group to ensure that more older adults benefit.

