##### Adherence and Security

If 9 weeks and more reach to the target activity levels during the entire intervention period, it will be considered as good adherence. The incidence of adverse events, including falls and all-cause hospital admissions, will be assessed by patient self-report.

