### Statistical Analysis

Categorical variables will be described by frequency and percentage. Continuous variables will be described by means and standard deviations. Social demographic and clinical data between the groups will be presented using appropriate descriptive statistics and evaluated for homogeneity using independent *t*-test, Mann-Whitney, chi-square, and Fisher’s exact tests, as appropriate. The differential changes of the primary and secondary outcomes at T1 and T2 concerning T0 between the two groups will be assessed using generalized estimating equations (GEE). The baseline variable will be adjusted, and group effects, time effects, and interaction effects will be observed. DSS statistics 25 will be used for data analysis, and *P* < 0.05 will be considered statistically significant.

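### Read literally, the plan gives controls the same guidance before the 24-week assessment, so the week-24 contrast could not be a randomised test of the lingering effect

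*Protocol article*

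**What the plan says.** The Introduction of the protocol article gives a second aim beside the main effect: to "observe the lingering effect in community-dwelling frail older adults".

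Study Design then sets out the phases in order:

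- Group 1: "Participants in the first group will receive a 12-week IERMS-based intervention".
- Group 2: "participants in the second group will receive a 12-week conventional care".
- Next phase: "Then, there will be a 12-week follow-up".
- Assessments: "Data will be collected at baseline, 12 and 24 weeks".
- After a pointer to Figure 1, the paragraph closes with: "After the intervention, the same guidance will be given to the second group to ensure that more older adults benefit".

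Statistical Analysis applies generalized estimating equations to "The differential changes of the primary and secondary outcomes at T1 and T2 concerning T0 between the two groups". With three collection times, T0, T1 and T2 must be baseline, week 12 and week 24. That section makes no provision for group 2 having received the guidance by T2.

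**The concern.** A between-group contrast at week 24 measures persistence only if the comparison group is still on usual care at that time. If controls have had the guidance in weeks 12 to 24, both arms have been exposed, and controls more recently. The contrast then mixes what group 1 has kept with what group 2 has gained.

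A lasting benefit could then show as a shrunken, absent or reversed difference and be reported as having faded. Week 24 is the only planned assessment after the intervention period has ended, so it is the only one that can speak to the lingering-effect aim. Once controls have received the guidance, the usual-care comparator at week 24 is gone and no later analysis restores it.

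**Working it through.** **Timing, from the text**

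1. Study Design attaches the intervention to a 12-week period and places a 12-week follow-up after it. The two phases are consecutive: weeks 0–12 and weeks 12–24.
2. Group 2's conventional care is also given as 12 weeks, not 24.
3. Adherence and Security uses the word the same way. Good adherence is defined as "If 9 weeks and more reach to the target activity levels during the entire intervention period", which fits a 12-week period that excludes follow-up.
4. The offer to group 2 is tied to the end of the intervention, not to the end of follow-up or of the study. No visible sentence defers it past week 24.

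Taken literally, the offer therefore opens at week 12, ahead of the T2 assessment.

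**The plan's own figures**

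Calculation of Sample Size gives power 0.90, error probability 0.05, 50 per group, 15% dropout and a total of 120.

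- Dropout: 100 / (1 − 0.15) = 117.6, so 118. This is within 2 of the stated 120, which also equals 6 centers × 20.
- The 50 per group cannot be reproduced, because the article gives a 20% difference in walking speed without an SD or a reference mean. The effect that 50 per arm can detect can be back-solved. The normal approximation, two-sided, is d = (1.960 + 1.282) / √(50/2) = 3.242 / 5 = 0.648. The t-test gives 0.655 two-sided and 0.589 one-sided. The article does not state the sidedness.

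The point about timing does not depend on these figures. The value 0.655 only gives the illustration a scale. It comes from walking speed, a secondary outcome; the primary outcome is the Timed Up & Go test.

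**What the week-24 contrast would estimate**

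Let d be the week-12 effect, r the share that group 1 retains at week 24, and c the share that group 2 gains by week 24. Then:

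week-24 contrast = (r − c) × d

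Neither r nor c is in the documents. With d = 0.655, 50 per arm and a two-sided test at 0.05:

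| r (group 1) | c (group 2) | Contrast, SD | Probability of significance |
|---|---|---|---|
| 1 | 0 | 0.655 | 0.90 |
| 1 | 0.25 | 0.49 | 0.68 |
| 1 | 0.50 | 0.33 | 0.37 |
| 1 | 0.75 | 0.16 | 0.13 |
| 1 | 1 | 0 | 0.05 |
| 0.75 | 1 | −0.16 | 0.13 |
| 0.50 | 1 | −0.33 | 0.37 |

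In the last two rows the contrast favours control, so significance there would be in the wrong direction. With the one-sided value d = 0.589, the contrasts for r = 1 and c = 0.25, 0.50, 0.75 and 1 are 0.589 × (1 − c) = 0.44, 0.29, 0.15 and 0.

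Two opposite situations give the same answer. Full persistence with full control gain (r = 1, c = 1) gives 0, and so does no persistence against untreated controls (r = 0, c = 0). The between-group contrast alone cannot separate them.

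**The case against.** The strongest reply is that the timing is inferred. The sentence names no week. It closes a paragraph that has already set out the full 24-week schedule, and its stated reason is sharing the benefit, so it can be read as an offer made once the trial is over. Figure 1, cited just before it, is not available here and may settle the matter. This stands: a reader might infer that the comparator is certainly lost at week 24, and the documents do not support that. If the authors meant after week 24, the fault is unclear wording only. It still needs correcting, because staff at six centers who follow the text would end the control condition at week 12.

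Three further limits also stand:

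- **Content of the offer.** A reader might infer that both arms will have had the whole programme. The article says only that the guidance will be the same. Platform Delivery lists guidance as one of four functions of the system, and nothing says that controls receive insoles, app and weekly plans, or for how long. A lesser package would dilute the contrast rather than cancel it.
- **Whether any effect can be seen.** It would be too strong to say that the lingering effect cannot be observed at all. Group 1's own change from week 12 to week 24 remains visible, although it is not a randomised contrast.
- **Validity of early versus delayed.** That comparison is still randomised. It answers a different question and needs the right label.

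That the article is condensed is not an answer. The point rests on a stated sentence that, carried out as worded, conflicts with the stated aim and analysis.

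**Conclusion.** The concern holds conditionally. On the literal reading of Study Design, controls receive the guidance between weeks 12 and 24. The T2 between-group contrast then compares early with delayed intervention and cannot serve as a randomised test of the lingering effect. The comparison at week 12 is sound on any reading.

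The documents do not fix the size of the bias. Under the illustrative assumptions (two-sided test, 50 per arm, d = 0.655, full retention in group 1), it runs from a loss of about a quarter of the contrast, when controls gain 25% of the effect, to a loss of all of it when they gain 100%. The sign turns only if group 1 retains less than controls gain. A claim that the contrast will vanish or reverse would need full or near-full control gain, which nothing in the article establishes.

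**What to change.** Reconcile the aim in the Introduction, the closing sentence of Study Design and the T2 comparison in Statistical Analysis by stating when group 2 is offered the guidance and what the offer contains. There are two consistent ways to do this:

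1. State that group 2 is offered the guidance only after its 24-week assessment is complete. The T2 contrast then remains intervention versus usual care. The cost is one sentence, and controls wait longer for the offer.
2. If the offer comes earlier, label the T2 contrast as early versus delayed intervention, make no between-group persistence claim from it, and take week 12 as the only randomised comparison with usual care. Group 1's change from week 12 to week 24 can be described as a within-group observation. The cost is the randomised claim of durability.

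If Figure 1 already shows the timing, the text should be brought into line with it.

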**FIGURE 1 F1:**
[figure not shown]
Flow chart of the experimental procedure.

### Participants

#### Ethics Approval

The research protocol was approved by the Human Research Ethics Committee of the School of Nursing, Jilin University (HREC 2020122001). All participants will provide a signed informed consent when entering the study.

#### Eligibility and Recruitment

Participants will be recruited from six centers at the same time. Once there are 20 samples in a certain community, they will undergo the next step. Inclusion criteria are ≥ 65 years old, meeting the FRAIL scale for frail status, and familiar with the use of smartphones and tablets or computers. Exclusion criteria are nerve dysfunction (stroke, Parkinson’s disease, or lower limbs) with paraplegia, serious cardiovascular disease, cognitive impairment, continuous joint pain, severe muscle bone damage, life expectancy < 6 months of serious illness, serious hearing or visual impairment, severe depression or anxiety, other major diseases affecting training safety, hospitalization, and involvement in other clinical studies during this study.

#### Calculation of Sample Size

Based on *a priori* power analysis (G*Power 3.1.9.3) using a power of 0.90 and error probability of 0.05, a sample size of 50 participants will be required for each group to detect an assumed 20% difference in walking speed between the two groups. In addition, with an assumption of 15% dropout rate, a sample size of 120 participants will be initially targeted.

#### Randomization and Blinding

From each center, 20 participants will be recruited and stratified by gender and age; then, they will be randomly assigned to the first or second group in a 1:1 ratio through a computer-generated randomized list. This task will be performed independently by individuals not involved in the research process. All researchers will be divided into two teams: one team will be responsible for the guidance of group 1, and the other team conduct routine education, they will be ignorant of each other’s content. Throughout the intervention, neither the participants nor the researchers conducting the intervention or the data collection will be aware of the grouping. The study designer and the staff responsible for allocation concealment and data processing will be not permitted to participate in the whole intervention.

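### Allocation is balanced on centre, gender and age, but the stated GEE names none of them: centre is absent, and gender and age enter only if an undefined baseline term covers them

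*Protocol article*

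**What the plan says.** Allocation is described under Randomization and Blinding: 20 people are taken from each centre and "stratified by gender and age; then, they will be randomly assigned to the first or second group in a 1:1 ratio", from a list made by computer. Eligibility and Recruitment adds that "Participants will be recruited from six centers at the same time". Six centres of 20 make the target of 120, so the natural reading is individual randomisation within centre, stratified by two further factors. Age bands and block sizes are not given.

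Under Statistical Analysis, changes from baseline at the two later visits "between the two groups will be assessed using generalized estimating equations (GEE"). The model terms are then given in one sentence: "The baseline variable will be adjusted, and group effects, time effects, and interaction effects will be observed". The baseline term is singular and undefined. The same section has the groups' demographic and clinical data "evaluated for homogeneity using independent" t-tests and the usual non-parametric and categorical tests.

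**The concern.** Randomisation within strata makes the arms more alike on the stratification factors than simple randomisation would. If those factors predict the outcome, the treatment estimate varies less from trial to trial than an unadjusted model assumes. A model without them leaves their variance in the error term, so intervals are too wide and the test runs below its nominal level. Age, gender and centre are plausible predictors of Timed Up & Go and gait in a trial of 120.

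The wording of the adjustment sentence also matters. A reader cannot tell from it whether gender and age are in the model, and no reading of it clearly brings in centre. With tests of baseline homogeneity planned alongside, it should be plain that the covariates are fixed by the design and not by what those tests show.

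**Working it through.** **Inputs from the protocol article.** Six centres of 20; 1:1 allocation; 50 per group, power 0.90, error probability 0.05 and 15% dropout (Calculation of Sample Size). The sidedness is not stated, so two-sided is assumed.

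**The plan's own figure.** The 50 per group cannot be reproduced, because the 20% difference in walking speed comes without a mean or SD. Solved backwards, the normal approximation gives d = (1.96 + 1.2816)/√(50/2) = 3.2415/5 = 0.648; a two-sample t-test gives 0.655. A 20% difference then implies an SD of about 0.20/0.655 = 31% of the mean. The dropout step does reproduce: 50/0.85 = 58.8, so 59 per arm or 118 in total, against a target of 6 × 20 = 120.

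**Assumptions not in the documents.** Let R² be the share of outcome variance, after baseline adjustment, that centre, gender and age explain. It is taken as 0.02 to 0.20. Exact balance within strata is assumed. The formulas are for one post-baseline time point and ignore the few degrees of freedom used.

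**Formulas if the factors are omitted.**
- Reported SE divided by true SE = 1/√(1 − R²)
- True type I error = 2 × [1 − Φ(1.96/√(1 − R²))]
- Power, factors omitted = Φ(1.2816/√(1 − R²))
- Power, factors included = Φ(3.2415/√(1 − R²) − 1.96)

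For R² = 0.20, √0.80 = 0.894. The SE ratio is 1/0.894 = 1.118. The type I error is 2 × [1 − Φ(2.191)] = 2.8%. Power is Φ(1.433) = 92.4% with the factors omitted and Φ(3.624 − 1.96) = Φ(1.664) = 95.2% with them included.

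| R² | SE too large by | Type I error | Power, omitted | Power, included | Points forgone |
|---|---|---|---|---|---|
| 0.02 | 1.0% | 4.8% | 90.2% | 90.6% | 0.3 |
| 0.05 | 2.6% | 4.4% | 90.6% | 91.4% | 0.8 |
| 0.10 | 5.4% | 3.9% | 91.2% | 92.7% | 1.6 |
| 0.20 | 11.8% | 2.8% | 92.4% | 95.2% | 2.8 |

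The last column was taken before rounding.

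**Simulation check.** A single-time-point linear model was run with 96 patients, six centres by gender by two age groups, blocked 1:1 allocation, d = 0.655 and 4,000 runs per setting. At R² = 0.20 the type I error was 3.2% with the factors omitted and 5.5% with them included; power was 91.3% and 94.2%. At R² = 0.05 power was 89.7% and 90.5%. The simulated powers sit slightly below the table because 96 patients were used, not 100: with R² = 0 both models gave about 89%. The direction and the gaps agree with the formulas.

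**The case against.** The strongest reply is that the article never says the design factors are left out. The baseline term could mean the baseline value of each outcome, or baseline characteristics in general, and Table 3 lists age and gender among the data collected at baseline. A condensed article commonly leaves the covariate list to a statistical analysis plan, which is not shown. This stands to the extent that a reader who infers that the analysis adjusts for the baseline outcome and nothing else goes beyond the text. It does not remove the point. The article states an adjustment rule and lists model terms, that list does not reflect the stated randomisation, and centre is missing on any ready reading.

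Three further replies limit the size:

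- If the term is the baseline outcome value, much of the effect of age and gender is probably already absorbed, so the low end of the R² range is the more plausible.
- Exact balance is a limiting case. Twenty per centre over two genders and even two age bands averages 20/4 = 5 per stratum, and no block scheme is given. Weaker balance moves the type I error back towards 5%.
- A reader might infer that the homogeneity tests will be used to pick covariates. The article does not say so; it uses them to compare the groups at baseline. After proper randomisation they test only chance, but they do not alter the GEE estimate, so this is secondary.

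**Conclusion.** The point holds as a mismatch between design and stated model, with a modest and conservative effect. If centre, gender and age are omitted, standard errors are about 1% to 12% too large and the true type I error is about 4.8% to 2.8%. This rests on an assumed R² of 0.02 to 0.20 and on balance within strata.

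Two stronger readings are not supported. One is that the omission leaves the trial short of power. At the effect implied by 50 per group, power with the factors omitted is still 90.2% to 92.4%; what is given up is about 0.3 to 3 points against the adjusted model. A figure such as 72% to 74% can be produced by assuming d = 0.5 with 51 per arm (120 × 0.85 = 102 completers), but that shortfall comes from the smaller assumed effect, which the article does not state. The 90% itself is the article's claim for walking speed; nothing here establishes it for Timed Up & Go, the primary outcome. The other reading is that a significant result would be suspect. The error runs the opposite way, so a positive finding is not undermined.

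The change is worth making because it is nearly free, not because the trial's conclusions would otherwise be at risk.

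**What to change.** Replace the adjustment sentence in Statistical Analysis with one that defines the baseline term and ties the model to the design. Each between-group GEE should include centre as a fixed effect with six levels, gender, age and the baseline value of the outcome, alongside group, time and their interaction. State that these covariates are specified in advance and are not chosen from the baseline homogeneity tests. With only six centres, a fixed effect suits centre better than using it as the GEE cluster. Baseline characteristics can be presented descriptively, without significance tests.

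The cost is a sentence or two and about seven degrees of freedom (5 for centre, 1 for gender, 1 for age as a single term) out of about 102 expected completers. No new data are needed, since centre, gender and age are already known at randomisation.

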### Intervention

#### Training Based on Intelligent Exercise Rehabilitation Management System

At baseline, all participants will undergo physical function, physical activity, psychology, and cognition assessments. These assessments will be repeated at 12 and 24 weeks. Participants in the first group will receive a pair of smart insoles and a patient-side APP installed on their phone and will learn all the functions of the system. According to the participants’ physical activity level at baseline, professional rehabilitation therapists will select the activity plan from the default scheme (Table 1); upload it to the cloud, which is the management data layer; and send the plan for the next week according to the participants’ weekly completion. If the activity goal of the week is not reached, the plan of the week will be continued. Once the current week’s activities are completed, the plan for the next phase will be carried out. Participants will choose the type of physical activity (Table 2) in the APP according to their preferences and choose the activity day of the week and the training time of each activity according to the target activity days. The system will automatically generate the particular week’s schedule according to participants’ choices and remind them at the time set by participants. At the end of each activity, participants will upload the daily completion of the activity and fill in the specific activity time for unfinished projects. They will have access to view the week’s activity plan at any time and generate the week’s activity schedule every Monday. During the workout, participants will be asked to wear smart insoles that monitor dynamic changes in gait parameters and synchronize them to the cloud in real time. In addition, patients will communicate with professionals through a short messaging service built into the APP and receive feedback within 24 h. The APP interface is shown in Figure 2. Before the start of each training, the user will receive a reminder as follows:

**TABLE 1 T1:** Weekly training schedule.

Current PA (min)	Target PA (min/w)	Mon.	Tue.	Wed.	Thur.	Fri.	Sat.	Sun.
0–30	≥30	Upload last week’s completion Make plans for this week	3 days,1 time/day, 10 min/time					
30–60	≥60		4 days,1time/d					
			1 time:10 min, 2–3 time:15 min, 4 time:20 min					
60–90	≥90		4 days, 1 time/day					
			1–2 time: 20 min, 3–4 time: 25 min					
90–120	≥120		5 days, 1 time/day, 25 min/time					

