### Quality Control

Our research group has established a team of experienced clinical nurses and rehabilitation therapists at a rehabilitation center in Changchun, China. Experienced clinical nurses and researchers from the team will be responsible for recruiting participants. Participants meeting the inclusion criteria will be screened, they will be informed of the study details by the investigator, and if they agree to participate, they will be asked to sign a consent form. If there is a complex clinical problem, our researchers, nursing specialists, and rehabilitation therapists will work together to find a solution.

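### Participants are described as blinded to their group, but only group 1 receives the app, take-home insoles and weekly plans, so the trial cannot be participant-blind as claimed

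*Protocol article*

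**What the plan says.** The Design paragraph of the Abstract reads: "This is a multicenter, three-blind, two-arm, and cohort randomized controlled study". Study Design repeats the label. Neither place says which three roles are meant.

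Randomization and Blinding names them: "Throughout the intervention, neither the participants nor the researchers conducting the intervention or the data collection will be aware of the grouping". The same section splits the researchers so that "one team will be responsible for the guidance of group 1, and the other team conduct routine education", each team not knowing the other's content. It also keeps the study designer and the staff handling allocation concealment and data processing out of the intervention.

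The Intervention section describes what group 1 gets: "Participants in the first group will receive a pair of smart insoles and a patient-side APP installed on their phone". These participants are taught the whole system. Therapists choose an activity plan for them and "send the plan for the next week according to the participants’ weekly completion". They also get timed reminders, report their completion and exchange messages with professionals.

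For the other arm, Study Design says that "participants in the second group will receive a 12-week conventional care". Routine Care fills this in as health education and a monthly telephone call, which all participants receive. Study Design adds: "After the intervention, the same guidance will be given to the second group to ensure that more older adults benefit". Under Quality Control, before signing consent, "they will be informed of the study details by the investigator".

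**The concern.** A claim that participants do not know their group tells the reader that expectation cannot differ between the arms. That matters here because much of the health profile is reported by the participants themselves. This covers activity (IPAQ), depression (PHQ-9), anxiety (GAD-7), sleep (PSQI, whose scored items are all self-reported), the fatigue item of the Fried score, and adverse events.

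IPAQ is the most exposed. Group 1 is set weekly targets in minutes of activity and reminded of them, and is then asked to recall time spent active.

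The primary outcome, Timed Up & Go (TUG), is walked at the participant's usual speed, and the gait test at a pace the participant chooses. Timing and sensor readings are objective, but the effort behind them is not shielded from expectation.

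If the blinding claim stands, a difference on these scales will be read as blinded evidence. The limitations in the Discussion concede that training logs are self-uploaded and activity amounts self-reported. They do not say that the people reporting know their treatment.

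**Working it through.** **1. Can a participant be unaware of the group?** This is settled by comparing sections of the article.

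| Feature during the 12 weeks | Group 1 | Group 2 |
|---|---|---|
| App on own phone | yes | none described |
| Insoles worn during training | yes | none described |
| Therapist-set weekly plan | yes | none described |
| Reminders and messaging | yes | none described |
| Health education, monthly call | yes | yes |
| Sham app, device or plan | not applicable | none described |
| Same guidance afterwards | not applicable | promised |

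Both arms come from the same 20 people at each centre, and candidates are told about the study before consenting. Whether one has the app and the weekly plan is in effect the allocation itself. No section describes hiding the hypothesis or the other arm's content from participants. The mutual ignorance of content is stated only for the two research teams.

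**2. Which claimed levels are affected?**
- Participants: contradicted by the table above.
- Researchers delivering the intervention: hard to sustain, since each team serves one arm.
- Data collectors: not contradicted by this comparison.
- Data-processing staff: kept out of the intervention; not contradicted.

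**3. What could it do to a self-reported scale? (illustration)**

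Inputs from the article: 120 participants, 1:1 allocation, 15% dropout, P < 0.05. Assumptions, not in the article: a two-sided two-sample t-test, zero true effect, and a reporting bias b in SD units.

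- The article's own target: 50 per group is 100, and 100 / (1 − 0.15) = 117.6, rounded up to 118; the stated 120 is in line with this. The 50 per group cannot be reproduced, because no mean or SD of walking speed is given, but nothing here depends on it.
- Analysed per arm: 60 × 0.85 = 51.
- Degrees of freedom: 2 × 51 − 2 = 100; critical value 1.984.
- Noncentrality: b × √(51/2). For b = 0.2 this is 1.010; for b = 0.3 it is 1.515.
- Rejection probability, from the noncentral t: 0.170 at b = 0.2 and 0.323 at b = 0.3, against 0.05 at b = 0.

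**4. Across several scales.** For four scales treated as independent:
- bias 0.2 SD: 1 − (1 − 0.170)⁴ = 0.53
- bias 0.3 SD: 1 − (1 − 0.323)⁴ = 0.79
- no bias: 1 − 0.95⁴ = 0.185

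Part of the first two figures is therefore plain multiplicity, and independence is implausible for mood, anxiety and sleep in the same people. With an assumed common correlation between 0.7 and 0.3, simulation gives roughly 34% to 45% at 0.2 SD and 55% to 69% at 0.3 SD, against roughly 13% to 18% with no bias. The single-scale figures are the ones to use.

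**The case against.** The strongest defence is that the authors may mean masking to the study hypothesis or to the other arm's content, not to the treatment received. The consent text is not shown, so it is an inference, not a documented fact, that every participant knows the allocation from the first day. That much stands. But the sentence claims unawareness of the grouping itself, and no masking of the hypothesis is described for participants. A fuller protocol could not make both the claim and the described intervention true.

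It is also fair to say that supervised exercise can rarely be blinded, that the affected scales are secondary, and that the primary outcome is a timed test. These points stand. The defect is a wrong description, not a failure to blind something that could have been blinded.

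A reader might infer more than the documents support:
- *That no blinding exists in the trial.* Blinding of data collectors and separation of data-processing staff are not disproved here. They could still protect stopwatch timing, grip strength and MMSE scoring.
- *That group 2 never wears insoles.* The contrast holds for the intervention. The Gait Parameters section and Table 3 schedule insole-based gait tests without limiting them to one arm.
- *That TUG and gait are either as exposed as questionnaires or a safe refuge from bias.* They are less exposed but not immune. A scripted pace instruction would standardise the tester without blinding the walker.
- *That a false positive on at least one scale has a 53% or 79% chance.* Those figures need independence and should not be used without the no-bias comparator and the correlation range shown above.

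**Conclusion.** The point holds for participants: the article asserts a blinding level that its own intervention rules out, and no other section resolves this. The conclusion rests on the text and on no figure.

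The size of any resulting bias is unknown. Assuming 0.2 to 0.3 SD on one self-reported scale, the false-positive rate would be about 17% to 32% in place of 5%, with 51 per arm and no true effect. On the scales, the bias would most plausibly favour group 1; for self-reported adverse events the direction is unclear. The sample size and the planned GEE analysis are unaffected. The wrong blinding claim must be corrected, because it changes how the self-reported outcomes may be read.

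**What to change.** 1. In the Abstract (Design) and in Study Design, replace the three-blind label with one that names only the roles that can be blinded: data collectors, with data-processing staff kept separate from the intervention, as Randomization and Blinding intends.
2. In Randomization and Blinding, state that participants are not blinded to allocation, and remove the intervention researchers from the blinded roles.
3. In Outcome Measures, identify IPAQ, PHQ-9, GAD-7, PSQI, the Fried fatigue item and self-reported adverse events as open-label outcomes, to be interpreted with that caveat.
4. In the limitations paragraph of the Discussion, add that self-report is unblinded, and that self-paced TUG and gait are less exposed to expectation but not immune.

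The cost is a change of wording in the protocol, and in the registry entry if it carries the same claim. No participants, staff, procedures or analyses are added. The trial will describe itself less favourably, but accurately.
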